## Abstract

**Background:**

Pulmonary rehabilitation (PR) is an effective intervention for the management of people with chronic obstructive pulmonary disease (COPD). However, available resources are often limited, and many patients bear with poor availability of programmes. Sustaining PR benefits and regular exercise over the long term is difficult without any exercise maintenance strategy. In contrast to traditional centre-based PR programmes, telerehabilitation may promote more effective integration of exercise routines into daily life over the longer term and broaden its applicability and availability. A few studies showed promising results for telerehabilitation, but mostly with short-term interventions. The aim of this study is to compare long-term telerehabilitation with unsupervised exercise training at home and with standard care.

**Methods/Design:**

An international multicentre randomised controlled trial conducted across sites in three countries will recruit 120 patients with COPD. Participants will be randomly assigned to telerehabilitation, treadmill and control, and followed up for 2 years. The telerehabilitation intervention consists of individualised exercise training at home on a treadmill, telemonitoring by a physiotherapist via videoconferencing using a tablet computer, and self-management via a customised website. Patients in the treadmill arm are provided with a treadmill only to perform unsupervised exercise training at home. Patients in the control arm are offered standard care. The primary outcome is the combined number of hospitalisations and emergency department presentations. Secondary outcomes include changes in health status, quality of life, anxiety and depression, self-efficacy, subjective impression of change, physical performance, level of physical activity, and personal experiences in telerehabilitation.

**Discussion:**

This trial will provide evidence on whether long-term telerehabilitation represents a cost-effective strategy for the follow-up of patients with COPD. The delivery of telerehabilitation services will also broaden the availability of PR and maintenance strategies, especially to those living in remote areas and with no access to centre-based exercise programmes.

**Trial registration:**

ClinicalTrials.gov: NCT02258646.

**Electronic supplementary material:**

The online version of this article (doi:10.1186/s12890-016-0288-z) contains supplementary material, which is available to authorized users.

## Background

Chronic obstructive pulmonary disease (COPD) is characterised by a persistent airflow limitation that is usually progressive [1]. Patients experience frequent acute exacerbations, characterised by worsening of respiratory symptoms [2] which may lead, in the worst cases, to a hospital admission [3]. COPD poses a substantial burden on healthcare budgets. The largest part of the health service expenditure is for hospitalisations and emergency department (ED) presentations, which commonly occur in the latter stages of the disease [4]. Moreover, prior hospitalisations represent a risk factor for rehospitalisation in patients discharged after a severe exacerbation [5]. Hospital admissions for exacerbations do not only represent a burden for the healthcare system, but have also a negative impact on patients, who experience reduced physical activity, decreased exercise performance [6], and impaired quality of life, even in mild stages of the disease [7]. Dyspnoea, the most commonly reported symptom during acute events, is associated with anxiety and depression [8]. Importantly, reduced physical activity is the strongest predictor of mortality in patients with COPD [9].

Pulmonary rehabilitation (PR) is an evidence-based, multidisciplinary, and comprehensive intervention for the management of COPD [10–12]. The main goal is to improve the physical and psychological condition and to promote long-term adherence of health-enhancing behaviours [13]. Exercise training is the cornerstone of PR, aiming to improve physical capacity and ability to perform activities of daily living. Other components include patient assessment, behavioural change, education on self-management, and psychosocial support [13]. PR improves dyspnoea, physical performance, quality of life [10], and is effective in reducing use of healthcare resources [14]. However, the short-term benefits diminish over the succeeding 12 months without an effective maintenance strategy [15]. Sustaining long-term adherence to exercise training is difficult due to variation in day to-day condition, exacerbations, hospital admissions, and transportation problems [16]. Key factors which promote exercise maintenance include professional support, review of exercise intensity, goal setting, social support, positive personal attributes, and the availability of exercise programmes with regular supervision [16]. Only a few investigators have explored maintenance strategies to sustain the benefits of PR over the long term, with inconsistent results [17–20].

Telemedicine has the potential to improve access to PR and support long-term exercise maintenance strategies. Telerehabilitation is the use of information and communication technologies to provide rehabilitation services remotely to people in their homes or other environments [21]. In contrast to traditional centre-based programmes, undertaking PR within the home environment may promote more effective integration of exercise routines into daily life over the longer term [22]. Evidence of the use of telemedicine in PR is still limited [13]. A recent review showed that telemedicine was effective in increasing physical activity levels in patients with COPD [23]. A few studies, most of which uncontrolled, showed promising results for short-term telerehabilitation interventions in regards to feasibility, safety, exercise capacity, and health-related quality of life [24–29]. However, only one uncontrolled pilot study trialled a long-term telerehabilitation intervention for patients with COPD [30]. This study demonstrated positive outcomes in terms of exercise maintenance, physical performance, health status and quality of life [31]. Importantly, long-term adherence was supported by experienced health benefits, self-efficacy, emotional safety, and maintenance of motivation [32]. Larger controlled trials are needed to explore the long-term effects of telerehabilitation in COPD.

Developing new cost-effective ways to sustain regular exercise over the long term and broaden the applicability and availability of PR is an important goal in the COPD management. The aim of this study is to compare long-term telerehabilitation of COPD patients consisting of exercise training at home, telemonitoring, and self-management, with unsupervised exercise training at home and with standard care. We hypothesised that long-term telerehabilitation will reduce the number of hospital readmissions and improve patient’s level of physical activity, health status and quality of life. The results from this study will provide decision makers, as well as practitioners, evidence on whether telerehabilitation interventions might be added to the current offer of traditional PR programmes and maintenance strategies.

## Methods/Design

### Design

An international multicentre randomised controlled trial (RCT) conducted across sites in three countries (Norway, Australia, and Denmark), where 120 patients with COPD are randomly assigned to three arms (telerehabilitation, treadmill, control) in a 1:1:1 ratio and followed up for 2 years. The trial is restricted to patients who have volunteered and provided written informed consent in accordance with the Declaration of Helsinki. The trial received approval from the Regional Committee for Medical and Health Research Ethics in Norway (2014/676/REK nord), the Alfred Hospital Human Research Ethics Committee (289/14), and the North Denmark Region Committee on Health Research Ethics (N-20140038). The protocol of this RCT fulfils the Standard Protocol Items: Recommendations for Interventional Trials (SPIRIT) guidelines (Additional file 1).

### Eligibility criteria

To be eligible for enrolment, participants must have the following inclusion criteria: 1) a diagnosis of COPD, based on an FEV_1_/FVC ratio < 70 % [33], 2) moderate, severe or very severe airflow limitation, with forced expiratory volume in 1 s percentage (FEV_1_ % of predicted) < 80 %, 3) at least one COPD-related hospitalisation or COPD-related ED presentation in the 12 months prior to enrolment, 4) aged between 40 and 80 years, and 5) capable of providing signed written informed consent.

Participants are excluded if they have at least one of the following criteria: 1) attendance at a rehabilitation programme in the 6 months prior to enrolment; 2) participation in another clinical study that may have an impact on the primary outcome, 3) deemed by the healthcare team to be physically incapable of performing the study procedures, 4) presence of comorbidities which, in the opinion of the healthcare team, might prevent patients from safely undertaking an exercise programme at home (for example severe orthopaedic or neurological impairments, severe cognitive impairment), and 5) home environment not suitable for installation and use of rehabilitation and monitoring equipment. Potential participants are not excluded on the basis of their existing home Internet access, as this can be provided by the study.

### Randomisation

Randomisation is stratified by centre and disease severity (FEV_1_ < 50 % vs. FEV_1_ ≥ 50 %) to preserve homogeneity between arms with regard to severity of clinical status. Randomisation is web-based and performed via the WebCRF program developed by the Unit for Applied Clinical Research at the Norwegian University of Science and Technology in Trondheim. The tool uses a computerised block randomisation, and the size of the first, smallest and largest blocks is established based on the total number of patients expected to be included in the study. The randomisation sequence generated is concealed from the study team by the program. The same WebCRF program is used to fill out electronic case report forms (CRFs). This allows patient data from several centres to be entered into the same database.

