### Recruitment and study procedures

At enrolment, a clinical assessment is performed for all the patients by appropriately trained study personnel blinded to group allocation. Participants are asked to perform spirometry, the 6-min walking test [36] and complete the study questionnaires (Table 1). Participants are also provided brochures containing information about PR, physical activity and training, diet, self-management, motivation and lifestyle changes, smoking cessation and oxygen therapy.

**Table 1 Tab1:** Data collected at baseline and follow-up visits

Data collected	Baseline	6-month	1-year	2-year
Clinical history and patient’s characteristics	X			
Pharmacological treatment	X			
Spirometry	X	X	X	X
6-min walking test	X	X	X	X
MMRC Dyspnoea Scale	X	X	X	X
COPD Assessment Test	X	X	X	X
EQ-5D Health Questionnaire	X	X	X	X
Generalised Self-Efficacy Scale	X	X	X	X
Hospital Anxiety and Depression Scale	X	X	X	X
Level of physical activity	X	X	X	X
Healthcare utilisation		X	X	X
Patient Global Impression of Change		X		

After enrolment, patients in the telerehabilitation and the treadmill arms undergo a supervised session on the treadmill with an experienced research physiotherapist to learn how to safely exercise at home, receive information on how to make progress in the programme and are given the opportunity to clarify any questions related to equipment management. Patients in the telerehabilitation arm also receive training on the use of the study website. A test videoconferencing session is also performed by the local research team to guarantee proper equipment functioning. Patients can always contact the research team in case of technical issues.

At 6-month, 1-year and 2-year, patients undergo a clinical reassessment and are asked to complete the study questionnaires (Table 1). During data collection patients are encouraged to continue participating in the study. Patients are discharged from the trial after 2 years, those in the telerehabilitation and the treadmill arms can keep the equipment at the end of the study.

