### Statistical analysis

Descriptive statistics at baseline will be reported as means ± SD for normally distributed continuous variables, or medians with 25–75th percentiles in the case of skewed distribution. Normality of distribution will be tested by means of the nonparametric Kolmogorov-Smirnov test. An intention-to-treat analysis will be performed on all randomised subjects to provide unbiased comparisons among groups and avoid the effects of dropout. The primary outcome and related secondary outcomes will be measured through the Incidence Density, defined as the number of events in a group divided by the total person-time accumulated during the study in that group [44]. Differences between study arms will be tested by the Comparison of Incidence Rates. A two-sided test and a significance level of *α* = 0.05 will be used. All events from the day after randomisation to patient exit/death will be included. Other secondary outcomes will be measured as changes from baseline to all assessment time points. Changes of the secondary outcomes will be tested by use of linear mixed models, which allow accounting for repeated measures collected in a longitudinal design. Moreover, linear mixed models deal better with dropouts that other methods used for repeated measures, and use of imputation techniques for missing data is not necessary. A *p*-value <0.05 will be considered significant for all tests. All statistical analyses will be performed by using IBM SPSS Statistics.

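### The primary test is fixed as an unadjusted comparison of pooled group rates, although randomisation is stratified and the protocol itself calls prior admissions prognostic

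*Protocol article*

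**What the plan says.** The Randomisation section of the protocol article says "Randomisation is stratified by centre and disease severity", with FEV1 split at 50 %.

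The Statistical analysis section measures the primary outcome (hospitalisations plus ED presentations) by incidence density, "defined as the number of events in a group divided by the total person-time accumulated during the study in that group". It then fixes the test: "Differences between study arms will be tested by the Comparison of Incidence Rates". No stratum or covariate is named for this test.

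On prognosis, the Background says that "prior hospitalisations represent a risk factor for rehospitalisation in patients discharged after a severe exacerbation", and the Discussion makes the same point. The Eligibility criteria require "at least one COPD-related hospitalisation or COPD-related ED presentation in the 12 months prior to enrolment". Table 1 lists "Clinical history and patient’s characteristics" at baseline but marks healthcare utilisation only at 6 months, 1 year and 2 years. Under Outcome measures, events are to be taken from hospital records in Australia, regional systems in Denmark and national registries in Norway.

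For the remaining secondary outcomes: "Other secondary outcomes will be measured as changes from baseline to all assessment time points", and "Changes of the secondary outcomes will be tested by use of linear mixed models". The covariates of those models are neither listed nor excluded.

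**The concern.** Two pooled rates, each a total of events over a total of person-time, leave no place for a stratum or a patient-level covariate. The design treats centre and severity as important enough to balance, and the named test then drops both. Previous events, which the protocol describes as prognostic, are neither a stratification factor nor a covariate. With 40 patients per arm, a chance imbalance in event history therefore passes uncorrected into the primary rate ratio.

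At stake are the precision of the primary comparison and its robustness to such an imbalance. The named method also treats all events as if they came from patients of equal risk. This matters because covariates help only when the variance recognises that patients differ.

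**Working it through.** **1. The plan's own figure.** Inputs from the Sample size section: control rate 2 per person-year, rate ratio 0.60 (so 1.2 per person-year), power 95 %, α 0.05. The test is two-sided (Statistical analysis).

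Person-years per group = (1.960 + 1.645)² × (2 + 1.2) / (2 − 1.2)² = 64.97, rounded up to 65. The stated figure reproduces. It is a pure Poisson calculation, with no between-patient variance.

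**2. Follow-up per patient.** If 20 % drop out uniformly over 2 years, each dropout loses 1 year on average. Mean follow-up is 2 − 0.2 × 1 = 1.8 years, or 40 × 1.8 = 72 person-years per arm. On the plan's assumptions, power at 72 person-years is 96 to 97 %.

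**3. What adjustment can remove.** Let k be the between-patient dispersion among enrolled patients. The document gives no value, so k is assumed. Then

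Var(log rate ratio) = [1/(2 × 1.8) + 1/(1.2 × 1.8) + 2k] / 40 = [0.278 + 0.463 + 2k] / 40.

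Covariates act only on the 2k term. If they explain a fraction f of it, the share of variance removed is 2kf / (0.741 + 2k):

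| k | f = 0.2 | f = 0.5 |
|---|---|---|
| 0 | 0 % | 0 % |
| 0.25 | 8 % | 20 % |
| 0.5 | 11 % | 29 % |
| 1 | 15 % | 36 % |

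At k = 0, the plan's own assumption, nothing is gained.

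**4. How much a prior-year count might explain.** These are illustrative simulations with 40 patients per arm, gamma-distributed patient risk, at least one prior-year event, an assumed prior-year rate of 1.5 and 20 % uniform dropout. Here k applies before selection on a prior event. A negative binomial model with the log prior-year count is compared with one without it.

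- Fully persistent patient risk: the median standard error fell from 0.182 to 0.167 at k = 0.5 and from 0.205 to 0.174 at k = 1. The variance ratios are (0.167/0.182)² = 0.84 and (0.174/0.205)² = 0.72, a reduction of 16 % and 28 %. A separate run gave 14 % and 27 %.
- Fully persistent risk, k = 0.25: 7 %.
- Correlation 0.7 between prior and later risk: 6 % (k = 0.5) and 10 % (k = 1).
- Correlation 0.4: about 2 % in both cases.

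The range is about 2 to 28 %. Centre and FEV1 were not in these simulations, so no figure is available for the strata.

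**5. Why the variance must change too.** Under no effect, with rate 2 in both arms, the crude Poisson variance is (2/3.6)/40 = 0.0139. At k = 0.5 the actual variance is (2/3.6 + 1)/40 = 0.0389, which is 2.8 times larger. A nominal 5 % test then rejects when |Z| > 1.96/√2.8 = 1.17, about 24 % of the time. At k = 1 the ratio is 4.6 and the rejection rate about 36 %. A simulation that also selected patients on a prior event gave about 19 % and 26 %. With heterogeneity, the planned test understates its error, and adding covariates without changing the variance would not repair this.

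**6. Secondary outcomes.** For one follow-up visit with equal variances and correlation ρ with baseline, a raw change score has variance proportional to 2(1 − ρ) and a baseline-adjusted analysis to 1 − ρ². The ratio is (1 + ρ)/2. Adjustment lowers variance by 30, 25, 15 and 10 % at assumed ρ of 0.4, 0.5, 0.7 and 0.8.

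**The case against.** The strongest defence is that nothing here is invalid. Centre and severity are balanced by design, the unadjusted rate ratio is a legitimate estimate under randomisation, and adjusting for a prognostic count is a gain in efficiency and not the repair of an error. That stands as regards bias. It does not remove the mismatch between a stratified design and a test that cannot use the strata, and it does not cover prior events, which the design leaves to chance.

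Several stronger readings are tempting, and the document does not support them:

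- A reader might infer that a fixed share of variance, such as 15 to 30 %, is being wasted. That range needs favourable assumptions about k, ρ and the persistence of risk, none of which the article gives. It also compares two negative binomial models when the article names neither. If patients do differ, the first fault of the planned test is an understated standard error.
- A reader might infer that the trial already holds the prior-year counts. Eligibility verifies only one COPD-related event or more, the primary outcome is not restricted to COPD-related events, and Table 1 has no baseline utilisation item.
- A reader might take prior admissions as the strongest predictor named. The Background calls them a risk factor; it calls reduced physical activity the strongest predictor, and of mortality.
- A reader might conclude that baseline scores are ignored in the secondary analyses. The mixed-model covariates may sit in a document not shown. A mixed model that treats baseline as one of the repeated measures, with a common mean, is about as efficient as baseline adjustment in large samples and is not ruled out. Regression to the mean affects all arms equally in expectation, so it does not bias the comparison between arms.

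**Conclusion.** The point holds for the primary analysis. The article names a specific method, an unadjusted comparison of pooled rates, which cannot reflect the stratified randomisation or a factor that the protocol itself regards as prognostic. A better analysis is available at little cost.

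The size of the benefit is uncertain. It is zero without between-patient heterogeneity and about 2 to 28 % of the variance of the log rate ratio in illustrative simulations with assumed k of 0.25 to 1 and varying persistence of patient risk. It is realised only with a variance that allows for overdispersion. The differences in event rate between countries that would make centre informative are plausible, given three record systems, but are not shown.

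For the secondary outcomes, including baseline and strata is a sensible specification to confirm. The article contains no error on that point.

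**What to change.** Replace the primary test in the Statistical analysis section with a count regression: negative binomial, or Poisson with robust variance, with log person-time as offset and arm as the factor of interest. Include centre (country if centres are small) and FEV1 stratum. Add, as a pre-specified covariate, the log number of hospitalisations and ED presentations in the 12 months before enrolment. Define that count as the outcome is defined and take it from the same record sources. The entry criterion makes it at least one, so the logarithm exists.

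For the secondary outcomes, state that the linear mixed models include the baseline value, centre, FEV1 stratum, visit and arm by visit.

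The cost is wording, plus extracting the look-back count from records the trial already plans to use and listing it as a baseline item in Table 1. No new data are needed from patients. The article reports recruitment as continuing, so the covariates can be fixed before outcome data are examined by arm.

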### Interventions

#### Telerehabilitation arm

Patients in the telerehabilitation arm are offered an integrated intervention consisting of exercise training at home, telemonitoring, and self-management. The equipment includes: a) a treadmill (Sportsmaster T2 in Norway, Sportsmaster T3i in Denmark, Reebok ZRK1 in Australia), b) a pulse oximeter (Nonin 9570/9571), c) a tablet computer (Apple iPad Air), and d) a holder for the tablet computer (RAM) (Fig. 1). The feasibility of using such equipment was tested in a previous pilot study [30]. Videoconferencing is performed through Acano™ due to its ability to connect the participant’s tablet to videoconferencing protocol H.323 and Session Initiation Protocol (SIP) standards-based systems, desktop computers or mobile clients. Communication is performed with Advanced Encryption Standard (AES) encryption and features multiconferencing.

